### Setting

This trial will be conducted in a nongovernment organization (NGO) in Hong Kong. The NGO has a large catchment area covering three districts in Hong Kong with >500,000 inhabitants. Annual official statistics indicate that these 3 districts have consistently higher rates of IPV among all 18 districts in Hong Kong [39].

### Recruitment

We will adopt the same recruitment strategies successfully used in our previous trials in the same community [40]. These recruitment strategies include conducting promotional sessions in the host NGO community center and its numerous outreach sites, providing recruitment talks in the neighborhood public housing estates where IPV is prevalent, enlisting the help of school principals to facilitate subject recruitment from among the mothers of the students, recruiting subjects from those participating in the well-established community networks, and advertising this project in the newsletters published by the host NGO.

For recruitment, a face-to-face meeting will be arranged in a private area with each potential participant. Following a well-established protocol to ensure the woman’s safety and consistency of the recruitment procedures [40], one of our trained research assistants will explain the trial to the woman, including the nature of a randomized, wait-list controlled trial; her rights as a research subject; and the need for obtaining blood specimens from her. If she agrees, she will sign a written consent form. The C-AAS will then be administered. Women determined to be “not abused” according to the C-AAS results will be thanked for their interest and assured that no further contact will be made. Those determined to be “abused” and who meet the inclusion criteria will be enrolled in the study.

### Randomization and blinding

All eligible participants will be randomized to either the intervention or wait-list control group according to a list of random permutations prepared by block randomization performed by a person not involved in subject recruitment. The block size will be known only by the randomizer. The order of the allocation, which will not be altered, will be centrally controlled to avoid any bias in selection. The research assistants will call the central-control center to obtain the list of random permutations for the allocation.

The questionnaires will be self-completed by the women and numerically coded without revealing the group allocation of the participants. A list of the numerical codes and names of the participants will be kept separately and securely in the central-control center. The researchers conducting the measurement of telomerase activity and its modulating biochemical factors will be blinded to the group allocation.

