### Participants

Chinese women will be eligible to participate if they are:≥18 years of age,willing to undergo the qigong intervention,available for all testing points,receptive to random allocation, andconfirmed to have been abused by an intimate partner within the past three years based on the Chinese Abuse Assessment Screen (C-AAS).

Chinese women will be excluded if they:have participated in qigong training or other mind–body interventions within the previous 6 months,have serious medical conditions that might limit their participation in qigong exercise (based on our previous experience, such conditions include cancer, severe obesity, narcolepsy, major depressive disorder, and schizophrenia),have psychiatric disorders,use medication or other psychological intervention for stress, orhave been abused by someone other than their intimate partner.

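### Block concealment appears to rest on keeping one block size secret; a recruiter who sees the ordered allocation history could infer a constant size, so the list should use randomly varying blocks

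*Protocol article*

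**What the plan says.** All references are to the Protocol article.

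- **Randomization and blinding.** Allocation follows a "list of random permutations prepared by block randomization performed by a person not involved in subject recruitment". The block structure is protected by one statement: "The block size will be known only by the randomizer". On the sequence: "The order of the allocation, which will not be altered, will be centrally controlled to avoid any bias in selection". On delivery: "The research assistants will call the central-control center to obtain the list of random permutations for the allocation".
- **Recruitment.** The same role approaches the women: "one of our trained research assistants will explain the trial to the woman". Consent, the abuse screen and enrolment follow.
- **Blinding.** The section covers the laboratory side, "The researchers conducting the measurement of telomerase activity and its modulating biochemical factors will be blinded to the group allocation", and numerically coded, self-completed questionnaires. It states no blinding of the research assistants. Under Methods/Design the arms are immediate and delayed qigong, so allocation is evident once made.
- **Setting and Sample size.** One NGO; 240 women, 120 per arm.

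The article gives no block size, does not say whether the size is constant or varies, and mentions no strata.

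**The concern.** With equal allocation in blocks of one size, the arms are level at every multiple of that size. Someone who sees past assignments in order can therefore work out the size without being told. From then on, once one arm has used up its places in a block, the rest of that block is known in advance.

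Foreknowledge matters because entry leaves room for judgement and timing. One exclusion applies to women who "have serious medical conditions that might limit their participation in qigong exercise", and inclusion asks for willingness and availability at every testing point. A recruiter expecting a particular arm could bring forward or hold back particular women. Adjusting for the baseline value of the outcome would not remove selection on unmeasured traits such as motivation. In addition, the Instruments section places T0 after randomization, so the self-reported PSS and BDI-II baselines may be given once the arm is known.

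**Working it through.** **Inputs.** From the article: 240 women, 1:1 allocation, blocks, no strata stated. Assumed: block sizes of 4, 6 or 8 (10 and 12 as a wider range), one unbroken sequence, and an observer who sees every past assignment in order.

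**1. The plan's own figure.** The only stated design calculation is 113 per group (difference 0.075, SD 0.2, 80% power, 5% level taken as two-sided):

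n = 2 × (1.960 + 0.842)² × (0.2/0.075)² = 2 × 7.85 × 7.11 ≈ 112 per group.

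This agrees with 113, at which power is 80.5%. Only the total of 240 and the 1:1 ratio enter below.

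**2. Size known.** For a block of 2k, the expected share of assignments known with certainty is 1/(k+1). The accuracy of always guessing the arm with more places left is [k + (4^k / C(2k,k) − 1)/2] / (2k).

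- Size 4: 1/3, or 80 of 240; (2 + (16/6 − 1)/2)/4 = 0.708
- Size 6: 1/4, or 60 of 240; (3 + (64/20 − 1)/2)/6 = 0.683
- Size 8: 1/5, or 48 of 240; (4 + (256/70 − 1)/2)/8 = 0.666

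**3. Size constant but secret.** The observer starts with equal weight on sizes 2, 4, 6, 8, 10 and 12. Under size b, the chance that the next woman goes to intervention is (b/2 − intervention places used in the current block)/(places left in it). Each size is reweighted by how well it predicted each assignment. Each true size was simulated 200 times over 240 women.

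**4. Sizes varied at random.** The observer knows the set of sizes but not their order; again 200 lists of 240.

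| Scheme | Women until size identified with >95% probability, median (10th–90th percentile) | Assignments predictable with >95% certainty, all 240 | Best-guess accuracy |
|---|---|---|---|
| Constant 4 | 42 (36–60) | 30% | 71% |
| Constant 6 | 42 (42–63) | 22% | 68% |
| Constant 8 | 36 (11–78) | 18% | 67% |
| Random 4/6 | – | 5.4% | 69% |
| Random 4/6/8 | – | 2.5% | 68% |

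For constant sizes 10 and 12 the medians are 24 and 20 women, with 15% and 14% of assignments predictable.

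**5. Hand check for size 4.** Lists in blocks of 4 are also level at 8 and 12, so those sizes are never excluded outright; they only lose weight. After 36 women the odds of 4 against 8 are (70/36)⁵ = 27.8, and against 12 they are (924/216)³ = 78.3. With the other sizes already excluded, the probability of 4 is 1/(1 + 1/27.8 + 1/78.3) = 0.953. This matches the 10th percentile of 36.

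**6. What secrecy alone buys.** Step 2 minus step 3 gives 33 − 30, 25 − 22 and 20 − 18, or about 2 to 3 percentage points.

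**The case against.** A constant size is read from a singular noun. The article is condensed, and block length and variation are details that a full protocol or randomization document often holds. The section also has real safeguards: a list preparer outside recruitment, a secret size, and a central, unaltered order. Inference needs one person to follow the whole sequence, whereas the text speaks of several research assistants and many outreach sites. All women eventually receive qigong, which weakens any motive to steer. The delivery sentence, read literally, hands over the list itself, which would expose upcoming assignments whatever the block size.

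Much of this stands. A reader might infer that the plan fixes a single size, that allocation is generally predictable, or that steering is under way. The document supports none of these. The size and its constancy are not stated. About 70% of assignments stay short of 95% certainty even at size 4. There is no evidence of steering. A reader might also expect varying blocks to bring guessing back to 50%; they do not.

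What the objection does not remove is that the article chose to state its protection of the block structure, and that protection is secrecy of the size. An independent preparer and a central order do not prevent inference from past assignments. The literal reading of the delivery sentence is an added reason to rewrite it, since varying the blocks cannot help if the list is released.

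**Conclusion.** The point holds as a cheap improvement to a stated safeguard, not as a demonstrated error. If the size is constant and a recruiter sees the ordered history, secrecy gives little protection: for sizes 4 to 8, between 18% and 30% of the 240 assignments (about 44 to 72 women) are predictable with over 95% certainty. Randomly varying sizes bring this to about 5–6% (sizes 4/6) or 2–3% (4/6/8). The gain is in near-certain foreknowledge only, because best-guess accuracy remains about 68–69%.

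These figures rest on assumed block sizes, a single unstratified sequence and full sight of past assignments. If several assistants each see only part of the sequence, predictability would be lower. No resulting bias in telomerase activity, PSS or BDI-II has been quantified.

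**What to change.** In Randomization and blinding:

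1. Generate the central list with block sizes that vary at random, for example a mix of 4, 6 and 8, with the sizes and their order held only by the randomizer. Reword the sentence quoted above so that its subject is *Randomly varying block sizes*. If the sizes already vary, it is enough to say so.
2. Replace the delivery sentence with a statement that the centre gives one assignment per call, after consent and eligibility have been recorded, and does not give the list to recruiters. Without this the first change does not help.

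The cost is one setting when the list is generated and two sentences of text. Sample size and power are unchanged. If recruitment stops inside a block, the arms may differ by a few women: at most 4 with a largest block of 8 (8/2).

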### Sample size

Sample size calculation will be based on a primary comparison of telomerase activity levels between the intervention and control groups. Based on a previous study that examined the effect of qigong on telomerase activity [27], the standard deviation will be set at 0.2. As in the study by Ho et al. we anticipate approximately 0.05 to 0.10 units of improvement in telomerase activity secondary to qigong. Thus, 113 subjects per group are required to detect a difference of at least 0.075 units between the two groups with 80% power and a ≤5% chance of a false-positive error. Allowing for a small rate of attrition, 240 women will be recruited and randomly assigned to either the intervention group (treatment condition, n = 120) or the wait-list control group (control condition, n = 120).

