### Measurements

#### Instruments

The following study instruments with the exception of the C-AAS and demographic questionnaire will be administered at three time points: (a) preintervention (T0, baseline); i.e., upon entry into the study, after randomization but before intervention; (b) post-training (T1, 6 weeks later); i.e., upon completion of the 6-week group learning and practice session; and (c) postintervention (T2, 5.5 months later); i.e., upon completion of the entire qigong intervention program. The C-AAS and demographic questionnaire will only be administered at baseline.The five-item *C-AAS*, which has demonstrated satisfactory psychometric properties [42], will be used to screen potential participants for IPV. If a woman answers “yes” to being emotionally, physically, or sexually abused within the past three years and if the perpetrator is her former or current intimate partner, she is considered to be positive for IPV.The *CTS2*, which has been validated with satisfactory validity and reliability [43], will be used to measure the type and frequency of behaviors used by the perpetrator during partner conflict. This 27-item instrument contains 8 measures of psychological aggression, 12 measures of physical assault, and 7 measures of sexual coercion. How often each behavior occurred within the preceding year is indicated by 0 = not within the past year, 1 = once, 2 = twice, 3 = 3 to 5 times, 4 = 6 to 10 times, 5 = 11 to 20 times, and 6 = 21 or more times.The 10-item *PSS*, the most widely used psychological instrument for measuring the perception of stress [44], will be used to assess the degree to which situations in life have been perceived by the participant as stressful during the past month. The PSS contains six negative and four positive items, and the overall score is obtained by reversing the responses to the four positive items (i.e., 0 [never] = 4, 1 [almost never] = 3, 2 [sometimes] = 2, 3 [fairly often] = 1, and 4 [very often] = 0) and then summing the response scores across all scale items. The PSS score may range from 0 to 40.The *PCS* [45] will be used to assess the types and perceived effectiveness of each of the 13 specific strategies used by the participant in dealing with violence perpetrated by her intimate partner. The strategies may be classified as active or passive; e.g., seeking assistance from family or friends, confronting the partner, redefining the meaning of the situation, or using alcohol or drugs. Scoring is based on a four-point Likert scale: 1 (not at all helpful), 2 (not so helpful), 3 (somewhat helpful), and 4 (very helpful).The Chinese version of the *BDI-II* will be used to assess depressive symptoms experienced within the previous 2 weeks. This 21-item instrument has established construct validity and reliability for Chinese populations [46]. The score may range from 0 to 63, with 0 through 13 indicating minimal depressive symptoms, 14 through 19 indicating mild depressive symptoms, 20 through 28 indicating moderate depressive symptoms, and 29 through 63 indicating severe depressive symptoms.A *demographic questionnaire* will be used to elicit the following information: age of the participant and her partner, education level, place of birth, number of years living in Hong Kong, marital status, duration of the abusive relationship, number of children, employment status of the participant and her partner, financial hardship, receipt of comprehensive social security assistance, need for financial support, and history of chronic illness.

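### As worded, research assistants obtain the list of random permutations, which conflicts with the central control and secret block size stated just before it

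*Protocol article*

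**What the plan says.** Under Randomization and blinding, the article describes four steps:

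- Someone who takes no part in recruiting draws up a blocked list.
- On the size of the blocks, the article states: "The block size will be known only by the randomizer".
- The sequence is fixed and held centrally, and prevention of selection bias is given as the reason.
- On how staff come by the allocation, the article then states: "The research assistants will call the central-control center to obtain the list of random permutations for the allocation".

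Under Recruitment, at a private face-to-face meeting, "one of our trained research assistants will explain the trial to the woman". Written consent and the abuse screen follow, and no other staff are named for those steps. Then: "Those determined to be “abused” and who meet the inclusion criteria will be enrolled in the study".

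The article does not say whether a call yields one assignment or many. It does not say whether a woman must be registered before the call, or whether the callers are different people from the recruiters.

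**The concern.** Allocation concealment means that whoever enters a participant cannot know her group beforehand. Having an independent person prepare the sequence, holding it centrally and keeping the block size secret all serve that end. Handing the list to the recruiting role would undo it. An unalterable order does not help if the person choosing whom to approach or enter next can see the next slot.

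There is room here for choice at entry. Recruitment runs through talks, schools and community networks, and some eligibility criteria need judgement, such as willingness to undergo qigong, availability for all testing points, and medical conditions that might limit participation. The blinded assays and coded questionnaires protect measurement of outcomes, not entry into the trial. Adjusting for the baseline value of an outcome does not remove imbalance in unmeasured motivation or likely adherence. Selection of this kind would affect every outcome and could not be repaired after enrolment.

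**Working it through.** **1. Is any figure in the plan involved?** The plan gives none for concealment. Its one reproducible figure is the sample size, and the point does not touch it. The inputs, all under Sample size, are a difference of 0.075, 80% power, a 5% error rate (taken as two-sided), and: "the standard deviation will be set at 0.2".

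- Normal approximation: n = 2 × (1.960 + 0.842)² × 0.2² / 0.075² = 2 × 7.85 × 0.04 / 0.005625 ≈ 111.6, so 112 per group.
- Two-sample t-test: 112.6, so 113 per group, as the plan states.

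**2. The statements side by side.**

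| Statement in the article | What it requires | If assistants hold the list before enrolment ends |
|---|---|---|
| List prepared by someone outside recruitment | Recruiters do not know the sequence | The recruiting role has the sequence |
| Block size known to the randomizer alone | No one else can work it out | With a single block size, the running difference between arms returns to zero at each block boundary, so the size can be inferred |
| Fixed order under central control, against selection bias | The center alone sees the next assignment | The next assignment is visible outside the center |

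Read literally, the fourth statement cannot stand with the other three.

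**3. How predictable is the next assignment?** This is an illustration only. The article gives no block size, so sizes of 4 to 12 are assumed, with 1:1 allocation (120 and 120).

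Suppose someone knows the past assignments and the block size, and always guesses the arm with more places left in the block. With a and b places left, the expected number of correct guesses is

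f(a,b) = max(a,b)/(a+b) + [a/(a+b)]·f(a−1,b) + [b/(a+b)]·f(a,b−1), with f(0,0) = 0.

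For a block of 4, the four positions give 1/2 + 2/3 + 2/3 + 1 = 2.833, and 2.833/4 = 70.8%.

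| What is known | Share of assignments foreseen |
|---|---|
| Full ordered list, before enrolment ends | 100% of those still to be filled |
| Past assignments and block size; blocks of 4, 6, 8, 10, 12 | 71%, 68%, 67%, 65%, 64% |
| Neither list nor block size | 50% |

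A list covering only women already enrolled shows no future assignment. The first row therefore depends on when the list is released and how much of it.

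**4. From predictability to bias.** That step needs to know how often staff would act on foreknowledge and how strongly the women steered would differ in outcome. The document gives neither, so no figure is offered.

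**The case against.** The best defence is the surrounding text. Central control and a secret block size would be pointless if recruiters were meant to hold the sequence, and telephoning a center is the usual form of concealed allocation. Obtaining the list for the allocation may be loose wording for obtaining an assignment from it. The section also says that it is eligible participants who are randomized, and qigong is taught in groups, so release for a batch of women already enrolled is plausible. Recruiters and callers share a job title and are not shown to be the same individuals. Finally, a condensed article may leave call logging and release procedures to the full protocol.

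Most of this stands as an account of what was probably intended. It does not remove the point, because the complaint is not about missing operational detail. The article states a rule, and staff who followed it literally could break concealment.

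A reader might infer more: that concealment is in fact defeated, that all assignments are predictable, or that women will be steered to qigong. The documents do not support this. It would require the full list to be released before enrolment ends, to people who recruit and who act on it, and none of that is stated. A reader might also bring in the timing of baseline, which is taken "upon entry into the study, after randomization but before intervention". That is a separate point and is no evidence of failed concealment.

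**Conclusion.** The point holds as an internal contradiction in the stated allocation procedure. Followed literally, the sentence would damage concealment; read charitably, it misdescribes a sound procedure. Either way it needs correcting, and the text does not settle which applies.

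The loss of concealment is conditional on the list, or a part of it reaching beyond women already enrolled, going to staff who also recruit. Under that condition up to 100% of the remaining assignments are foreseeable, against 50% when nothing is known. The direction and size of any bias in the treatment effect cannot be estimated. The 113 per group and the total of 240 are unaffected.

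**What to change.** Replace the sentence about obtaining the list with:

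*After a woman has consented, been confirmed eligible and been registered with the central-control center, the research assistant calls the center, which releases only that participant's assignment; the list stays at the center.*

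This costs one sentence in the protocol and one instruction to a center that already exists. It needs no extra staff and changes neither the sample size nor the analysis. Randomly varying block sizes would be an optional addition. Moving baseline ahead of randomization is a separate question; this correction does not need it.

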### Intervention

The qigong intervention in this project is based on the intervention tested by our team members ([name], Ho) in an earlier study that involved participants with chronic fatigue and achieved positive outcomes [27]. The intervention comprises (i) group learning and practice: a 2-hour qigong exercise training session provided by a qigong master twice a week for 6 consecutive weeks (total, 24 hours), (ii) weekly group follow-up: a 1-hour qigong exercise session provided by a qigong master once a week for 4 consecutive months (total, 16 hours) after the group learning and practice, and (iii) self-practice: a 30-minute qigong exercise session performed by each individual participant once a day for the whole intervention period (total, 63 hours). Each participant will perform a total of 103 hours of qigong during the 5.5-month intervention period.

For each of the 2-hour qigong exercise training sessions during the 6-week group learning and practice periods, the activities will include (i) a brief introduction to the basic theories of traditional Chinese medicine and the physiology of mind–body connections, (ii) gentle movement or body stretching in a standing posture to facilitate a harmonious flow of *qi* along the energy channels, and (iii) qigong exercise training delivered by an experienced qigong master.

